## Abstract

**Background:**

Pulmonary vein isolation (PVI) is the cornerstone of atrial fibrillation (AF) ablation, yet outcomes remain suboptimal in persistent AF. With thermal energy, adjunctive left atrial posterior wall isolation (PWI) has shown inconsistent benefit, partly owing to limited lesion durability and esophageal safety constraints. Pulsed field ablation (PFA) may enable safer, more reproducible posterior wall lesion sets.

**Objective:**

This study aimed to compare PVI alone with PVI plus PWI using the FARAPULSE PFA system in symptomatic, drug-refractory persistent AF.

**Methods:**

PERSIST-PWI is an investigator-initiated, multicenter, open-label, parallel-group randomized controlled trial at approximately 60 sites in Japan. 500 patients with persistent AF (AF duration ≤3 years) will be randomized 1:1 to PVI alone or PVI + PWI. Pre- and postablation 3-dimensional mapping with OPAL HDx (FARAVIEW) is mandated. Follow-up includes visits at 3, 6, and 12 months with 12-lead electrocardiograms (ECGs), 24-hour Holter monitoring at 6 and 12 months, and biweekly plus symptom-triggered portable ECG transmissions.

**Results:**

The primary effectiveness endpoint is acute ablation success and freedom from clinically meaningful treatment failure from the end of an 8-week blanking period through 12 months, defined as documented AF/atrial flutter/atrial tachycardia (≥30 seconds on ambulatory monitoring or ≥10 seconds on 12-lead ECG), repeat ablation, electrical cardioversion, or initiation/escalation of class I/III antiarrhythmic drugs including amiodarone. Key secondary endpoints include AF burden, quality of life (Atrial Fibrillation Effect on Quality-of-Life questionnaire), and predefined safety events.

**Conclusion:**

PERSIST-PWI will provide randomized evidence on whether PFA-enabled PWI adds clinical benefit beyond PVI while maintaining safety in persistent AF, thereby informing contemporary ablation strategies.

Key Findings
▪In persistent atrial fibrillation (AF), routine posterior wall isolation (PWI) has shown inconsistent incremental benefit with thermal ablation, partly owing to limited lesion durability and esophageal safety constraints.▪Pulsed field ablation provides preferential myocardial injury with relative sparing of adjacent structures, potentially enabling safer and more durable posterior wall lesion sets.▪The PERSIST-PWI study is an investigator-initiated, multicenter randomized trial comparing pulmonary vein isolation (PVI) alone with PVI plus PWI using pulsed field ablation in symptomatic, drug-refractory persistent AF in Japan.▪Mandatory pre- and postablation FARAVIEW-guided mapping enables mechanistic assessment of lesion completeness and procedural reproducibility.▪Rhythm outcomes will be assessed using structured follow-up with Holter monitoring and biweekly or symptom-triggered portable electrocardiography transmissions.

## Introduction

Atrial fibrillation (AF) is an increasingly prevalent arrhythmia associated with stroke, heart failure, and impaired quality of life. Catheter ablation with pulmonary vein isolation (PVI) is highly effective for paroxysmal AF; however, in persistent AF, recurrence remains frequent even after apparently successful PVI,^1^^,^^2^ reflecting more advanced atrial remodeling and the presence of non–pulmonary vein (PV) substrates. Consequently, adjunctive strategies targeting additional atrial regions have been proposed,^3^, ^4^, ^5^ among which left atrial (LA) posterior wall isolation (PWI) has attracted particular interest because the posterior wall can participate in AF maintenance.^6^

Despite a compelling mechanistic rationale, randomized trials using thermal energy sources (radiofrequency or cryothermal) have not consistently demonstrated incremental benefit of routine PWI beyond PVI in persistent AF.^3^, ^4^, ^5^ This may be attributable to 2 major limitations: (1) incomplete or nondurable PV and posterior wall block owing to anatomic complexity and lesion discontinuity and (2) safety constraints, particularly the proximity of the posterior wall to the esophagus, which limits energy delivery and raises concern for collateral injury^7^^,^^8^—thereby restricting operators from creating sufficiently extensive and durable lesions in routine clinical practice.

Pulsed field ablation (PFA) is a nonthermal modality based on irreversible electroporation. It offers preferential myocardial injury with relative sparing of adjacent structures,^9^, ^10^, ^11^ potentially enabling wider lesion sets with improved safety margins. Contemporary data demonstrate high acute PVI success rates, low serious complication rates, and encouraging chronic durability of both PVI and PWI with PFA.^10^, ^11^, ^12^, ^13^ Accordingly, a key clinical question remains: do the technical and safety advantages of PFA translate into a clinically meaningful benefit of adding PWI to PVI in patients with persistent AF? This question cannot be answered without a dedicated randomized trial.

The PERSIST-PWI trial was designed to address this evidence gap by directly comparing PVI alone with PVI plus PWI performed with the FARAPULSE PFA system in Japanese patients with persistent AF.

## Methods

### Study design and population

PERSIST-PWI is an investigator-initiated, multicenter, randomized, open-label, parallel-group trial being conducted in Japan. Scientific oversight is provided by a physician-led steering committee. The steering committee consisted of [name] (Nihon University), [name] (The Jikei University), [name] (Tokyo Medical University), [name] (Hirosaki University), [name] (National Cerebral and Cardiovascular Center), and [name] (Kitasato University). The trial protocol was registered in the Japan Registry of Clinical Trials (jRCTs032250541; registered on December 1, 2025) and was approved by the central ethics committee at Nihon University Itabashi Hospital (clinical research judging committee; lead institution). In addition, study initiation at each participating site requires local approval by the site’s ethics committee and/or hospital director, as applicable (Supplemental Appendix). The research reported in this paper adheres to the ethical principles of the Declaration of Helsinki and applicable Japanese ethical and regulatory requirements and is designed and will be reported in accordance with the Consolidated Standards of Reporting Trials guidelines for randomized clinical trials. A written informed consent will be obtained from all participants before enrollment. Eligible patients will be randomized 1:1 to PVI alone (control) or PVI plus PWI (intervention) using the FARAPULSE PFA system.

### Trial oversight, event adjudication, and core laboratory

Scientific oversight is provided by a physician-led steering committee. Participant safety is overseen by an independent data and safety monitoring board, which periodically reviews unblinded safety data. Clinical events and key safety outcomes will be adjudicated by an independent clinical events committee (CEC) according to prespecified definitions.

To mitigate potential bias inherent to the open-label design, rhythm endpoints will be assessed by an independent arrhythmia core laboratory blinded to treatment assignment using electrocardiography (ECG)-based documentation collected per protocol (12-lead ECGs, Holter recordings, and portable ECG transmissions).

### Study population

Patients will be adults (≥18 years) with symptomatic persistent AF (continuous AF ≥7 days or requiring cardioversion) and an AF duration of ≤3 years, refractory or intolerant to at least 1 class I/III antiarrhythmic drug. The exclusion criteria include previous LA ablation (including PVI), LA diameter (LAD) of >5.5 cm, left ventricular ejection fraction of <40%, estimated glomerular filtration rate of <30 mL/min/1.73 m^2^, New York Heart Association functional class III/IV, major cardiovascular events within 90 days, secondary AF owing to reversible causes, conditions making LA instrumentation unsafe (eg, intracardiac thrombus), severe valvular disease or previous valve intervention, history of ventricular tachycardia/fibrillation, and contraindications to or inability to maintain anticoagulation (Table 1). The full inclusion and exclusion criteria are presented in Supplemental Table 1.

**Table 1 tbl1:** Key inclusion and exclusion criteria

Inclusion criteria
1) Age ≥18 y
2) Symptomatic persistent AF (continuous AF ≥7 d or requiring cardioversion)
3) AF duration ≤3 y
4) Refractory or intolerant to ≥1 class I/III antiarrhythmic drug
5) Eligible for catheter ablation with PFA and able to provide a written informed consent
6) Willing and able to comply with protocol-specified follow-up and rhythm monitoring
Key exclusion criteria (as defined in protocol)
1) Previous left atrial ablation (including PVI)
2) Left atrial diameter >5.5 cm
3) Left ventricular ejection fraction <40%
4) eGFR <30 mL/min/1.73 m^2^
5) NYHA class III/IV heart failure
6) Major cardiovascular events within 90 d
7) Secondary AF owing to reversible causes
8) Intracardiac thrombus or other conditions making left atrial instrumentation unsafe
9) Severe valvular disease or previous valve intervention
10) History of ventricular tachycardia/fibrillation
11) Contraindication to, or inability to maintain, anticoagulation

Summary of inclusion and exclusion criteria. (Full criteria are presented in Supplemental Table 1).

AF = atrial fibrillation; eGFR = estimated glomerular filtration rate; NYHA = New York Heart Association; PFA = pulsed field ablation; PVI = pulmonary vein isolation.

### Randomization and stratification

Randomization will be performed centrally using a minimization-based dynamic allocation method. Patients will be allocated 1:1 to the PVI-alone group or the PVI + PWI group, stratified by site, age category (<75 vs ≥75 years), and LAD (<45 vs ≥45 mm). The overall study design is presented in Figure 1.

**Figure 1 fig1:**
[figure not shown]
Overview of the PERSIST-PWI trial design. Adults with symptomatic, drug-refractory persistent AF (AF duration ≤3 years) are randomized 1:1 (N = 500) to PVI alone or PVI plus PWI using the FARAPULSE pulsed field ablation system. FARAVIEW-guided 3D mapping is performed before and after ablation. Rhythm follow-up includes clinic visits with 12-lead ECGs, scheduled Holter monitoring, and transtelephonic/portable ECG transmissions. The composite effectiveness endpoint is acute success and freedom from clinically meaningful treatment failure from the end of an 8-week blanking period to 12 months. 3D = 3-dimensional; AAD = antiarrhythmic drug; AF = atrial fibrillation; DSMB = data and safety monitoring board; ECG = electrocardiography; PV = pulmonary vein; PVI = pulmonary vein isolation; PW = posterior wall; PWI = posterior wall isolation; RF = radiofrequency; TTM = transtelephonic monitor.

### Ablation procedures

All patients will undergo PVI using the FARAPULSE PFA system (Boston Scientific Japan K.K.). Acute PVI success will be defined as entrance block in all attempted PVs. As a rule, PVI will be performed using a standardized lesion delivery strategy (“two-pair basket plus two-pair flower” configuration per PV). During LA dwell, intravenous unfractionated heparin will be administered as needed to maintain an activated clotting time of >350 seconds.

3-dimensional electroanatomic mapping with the OPAL HDx mapping system (FARAVIEW software module) is mandatory to obtain LA and PV morphology. Pre- and postablation mapping will be performed using either the FARAWAVE 2.0 NAV PFA catheter or the IntellaMap Orion mapping catheter, according to operator preference and site availability. In sites where the IntellaMap Orion catheter is not available, pre-/postmapping with the FARAWAVE 2.0 NAV PFA catheter alone will be permitted. When the IntellaMap Orion catheter is used, LA access may be obtained via the FARADRIVE steerable sheath or another sheath sized ≥8.5F, with careful attention to air embolism, and the sheath will be exchanged to the FARADRIVE steerable sheath before insertion of the FARAWAVE 2.0 NAV PFA catheter for PVI, per protocol.

In the PVI + PWI group, additional posterior wall “box isolation” will be performed between the left and right PVs using anatomically guided applications with the FARAWAVE 2.0 NAV PFA catheter in the flower configuration, as described in the instructions for use. Roof and floor lines will be created (roof line along the inferior aspect of the superior PVs and floor line along the superior aspect of the inferior PVs). Particular attention will be paid to achieving complete cranial coverage of the LA roof to minimize the potential risk of roof-dependent macroreentrant atrial tachycardia (AT), with lesion completeness verified by FARAVIEW-guided mapping. Energy will be delivered at 2000 V with duplicate applications at each site and 50% overlap.^14^^,^^15^

In the PVI-alone group, only PVI will be performed and no additional posterior wall ablation will be undertaken. Catheter manipulation will be performed within the PV ostium and antrum, with care taken to avoid unintended energy delivery to the posterior wall.

Acute PVI success and PWI success will be confirmed by demonstration of entrance block with the disappearance of local PV and posterior wall field potentials. Where technically feasible, pacing from the PVs and posterior wall may be performed to assess exit block at the operator’s discretion.

No protocol-mandated waiting period is required, consistent with the pragmatic study design; reassessment after a short waiting period may be performed per operator discretion and site practice. Intracardiac echocardiography and/or fluoroscopic guidance may be used according to site practice and operator preference, and their use will be recorded. Field tag–based contact metrics are available at participating sites and may be incorporated into procedural assessment when feasible using a standardized approach informed by previous field tag–based analyses.^16^ In addition, emerging impedance-based contact sensing technologies may be incorporated as they become clinically available and will be analyzed exploratorily when applicable.

Adjunctive radiofrequency ablation (eg, cavotricuspid isthmus ablation) will be permitted in both groups only for predefined clinical indications, including documented non-PV triggers, sustained AT, typical atrial flutter, or other safety-driven needs; all adjunctive ablation will be recorded in the electronic data capture system. Procedural characteristics, including total procedure time (skin to skin), fluoroscopy time, acute PVI success, acute PWI success (PVI + PWI group only), and the presence and location of adjunctive ablation, will be collected.

### Follow-up and rhythm monitoring

Patient follow-up will consist of outpatient visits at 3, 6, and 12 months after the index ablation (day 0), including clinical assessment, review of medications, and 12-lead ECG at each visit. The use of antiarrhythmic drugs during follow-up will be systematically recorded in both treatment groups regardless of initiation or dose adjustment. Rhythm monitoring will include protocol-mandated 24-hour Holter monitoring at 6 and 12 months. In addition, transtelephonic monitoring and symptom-triggered recordings will be performed using an Omron portable ECG device (HCG-8060T), which will be provided by the study team. Participants will be instructed to transmit recordings biweekly after discharge and additionally at the time of symptoms suggestive of arrhythmia. Portable ECG transmissions are intended to complement intermittent Holter monitoring and improve capture of clinically relevant recurrences in real-world follow-up.

### Quality of life

Quality of life will be assessed using the Atrial Fibrillation Effect on Quality-of-Life questionnaire and the EQ-5D-5L at baseline and at 12 months.

### End of study and safety follow-up

The observation period is 12 months after ablation, and adverse events (AEs) will be collected from the procedure through 12 months, with additional follow-up as needed until recovery or stabilization. The schedule of study assessments is presented in Table 2.

**Table 2 tbl2:** Schedule of study assessments

Observational items	Day −28 ∼ −1	Day 0	Day 1	3 mo ± 2 wk	6 mo ± 3 wk	12 mo ± 1 mo	Time of discontinuation	At the end of follow-up
Obtaining informed consent	○							
Background of study subjects	○							
Enrollment		○						
Physical examination and vital signs	○		○	○	○	○	○	○
Concomitant medications/therapies (including compliance information)	○	○	○	○	○	○	○	○
Assessment of symptoms (subjective symptoms)	○		○	○	○	○	○	○
ECG (12 leads)			○	○	○	○	○	○
24-h Holter monitoring (routine medical practice)					○	○		
TTM				Initiation∗	To continue	To continue		
Cardiac ultrasound (echocardiography)	○							
Blood tests (routine medical practice)	○		○					
Blood tests (hemolysis assessment)	○		○					
Urine tests (hemolysis assessment)	○		○					
Ablation procedure information		○						
Evaluation of adverse events/complications			○	○	○	○	○	○
Symptomatology and QOL assessment (AFEQT, EQ-5D-5L)	○					○		
Presence of recurrent AF (subjective/objective)			○	○	○	○		

Schedule of protocol-specified visits and assessments from screening through 12-month follow-up, including ECG-based rhythm surveillance, Holter monitoring, and transtelephonic/portable ECG transmissions.

AF = atrial fibrillation; AFEQT = Atrial Fibrillation Effect on Quality-of-Life; ECG = electrocardiography; QOL =quality of life; TTM = transtelephonic monitor.

∗ Visit should be 3 months to match the routine clinical visit. However, the usage of TTM shall be explained at the time of discharge from the hospital, and measurements will begin the day after discharge.

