Key secondary endpoints	1) Individual components of the primary composite endpoint 2) Time to documented AF recurrence 3) AF burden based on rhythm-monitoring data 4) Change in quality of life: AFEQT and EQ-5D-5L 5) Safety outcomes (see Supplemental Table 2 for definitions)
Exploratory endpoints	1) Association between posterior wall block durability and recurrence 2) Trajectories of hemolysis biomarkers and renal function 3) Prespecified subgroup effects (age, sex, BMI, LAD, AF duration, DR-FLASH score)

Overview of study endpoints. Detailed endpoint definitions and ascertainment procedures are presented in Supplemental Table 2.

AF = atrial fibrillation; AFEQT = Atrial Fibrillation Effect on Quality-of-Life; AFL = atrial flutter; AT = atrial tachycardia; BMI = body mass index; ECG = electrocardiography; LAD = left atrial diameter.

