### Statistical considerations

Sample size was informed by previous randomized trials of PWI using thermal energy sources (eg, STAR AF II,^3^ CAPLA,^4^ and other studies^5^^,^^17^^,^^18^), in which the 1-year freedom from atrial arrhythmia after PVI alone ranged from approximately 53% to 71% and incremental benefit of routine PWI was not consistently demonstrated. In contrast, contemporary PFA technology may enable more durable and safer posterior wall lesion sets, which could translate into improved clinical effectiveness.

Based on published PFA outcomes and supporting prospective data,^14^^,^^15^ the assumed 12-month freedom from the primary composite effectiveness endpoint was set at 60% for the PVI-alone group and 72.5% for the PVI + PWI group (absolute difference 12.5%). With a 2-sided type I error probability of .05 and 80% power, 224 participants per group (total 448) are required. To account for an anticipated 10% dropout rate, the planned enrollment is 250 participants per group, resulting in a total sample size of 500.

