Effectiveness analyses will be conducted according to the intention-to-treat principle. Safety analyses will be performed in all participants who received study treatment (safety set). For the primary composite effectiveness endpoint, time-to-event analyses will focus on the postblanking treatment failure component; acute ablation success will be summarized descriptively by group. Time-to-event outcomes will be analyzed using Kaplan–Meier methods and compared with the log-rank test; hazard ratios and 95% confidence intervals will be estimated using Cox proportional hazards models, with prespecified covariate adjustment as appropriate. Rhythm endpoint documentation will be reviewed by the blinded arrhythmia core laboratory, and major safety outcomes will be adjudicated by the independent CEC. Prespecified subgroup analyses (age, sex, body mass index, LAD, AF duration, DR-FLASH score^19^) will be assessed using treatment × subgroup interaction terms. Missing data will be handled primarily by complete-case analysis, with multiple imputation and sensitivity analyses considered if missingness is substantial, as specified in the statistical analysis plan. A single interim review is planned after approximately 1 year of enrollment and will be conducted blinded under the oversight of an independent data and safety monitoring board. No formal interim hypothesis testing for effectiveness is planned. Analyses will be performed using SAS software (version 9.4 or later, SAS Institute Inc, Cary, NC).

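### Quality of life is measured only at baseline and month 12, so a participant who leaves before the 12-month window has no post-baseline score for a key secondary endpoint

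*Protocol article*

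**What the plan says.** The Quality of life section of the protocol article fixes the timing: "Quality-of-Life questionnaire and the EQ-5D-5L at baseline and at 12 months". Table 2 (End of study and safety follow-up) agrees. Its row "Symptomatology and QOL assessment (AFEQT, EQ-5D-5L" is marked at screening and at 12 months and nowhere else. The 3-month, 6-month and discontinuation columns are blank in that row, as is the end-of-follow-up column.

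The discontinuation column is a real visit with data collection. Physical examination, medications, subjective symptoms, 12-lead ECG and adverse events are all marked there.

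Table 3 lists "Change in quality of life: AFEQT and EQ-5D-5L" among the key secondary endpoints. Statistical considerations states: "Effectiveness analyses will be conducted according to the intention-to-treat principle". The same paragraph adds: "Missing data will be handled primarily by complete-case analysis, with multiple imputation and sensitivity analyses considered if missingness is substantial", and refers to the statistical analysis plan for details. The sample-size paragraph allows for early leavers: "To account for an anticipated 10% dropout rate".

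**The concern.** The endpoint is a change score that needs a month-12 value, and the schedule offers one post-baseline occasion on which to obtain it. Whoever leaves before that occasion contributes nothing to the change score, even after attending a 6-month visit and a discontinuation visit. With complete-case analysis as the default, the comparison is in effect one of completers, although effectiveness is to be analysed by intention to treat.

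The trial is open-label and the outcome is patient-reported. Blinded core-laboratory review protects the rhythm endpoints. It does not protect a questionnaire score, or a decision to leave that may depend on allocation or on how the patient feels. If leavers fare differently from completers, and differently by arm, the completers' comparison is biased. The analysis plan, which is not shown, can choose an imputation method but cannot supply scores that were never collected.

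**Working it through.** **1. The plan's own figures.** Inputs from Statistical considerations: 60% and 72.5% free of failure, two-sided 0.05, power 80%, 10% dropout. The mean proportion is (0.60 + 0.725)/2 = 0.6625. The pooled-variance formula without continuity correction gives

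n = [1.960 × √(2 × 0.6625 × 0.3375) + 0.842 × √(0.60 × 0.40 + 0.725 × 0.275)]² / 0.125² = 224 per group after rounding up.

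This matches the plan. Then 224/0.90 = 248.9, so 249 per group, which the plan rounds to 250. The point below changes neither figure.

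**2. Table 2, row by row.**

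| Row | Visits marked |
|---|---|
| AFEQT and EQ-5D-5L | screening, 12 months |
| 12-lead ECG | Day 1, 3, 6 and 12 months, discontinuation, end of follow-up |
| Presence of recurrent AF | Day 1, 3, 6 and 12 months |

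**3. How many participants.** 10% of 250 = 25 per arm, or 50 of 500. This is an upper figure at that rate: it holds only if every dropout leaves before the window opens and completes no month-12 questionnaire. Over an assumed range of 5% to 20% dropout, the figure is 12.5 to 50 per arm (25 to 100 in total).

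**4. Precision.** The standardised difference detectable with 80% power is (1.960 + 0.842) × √(2/n). For n = 250 it is 0.251. For n = 225 (250 − 25) it is 0.264. The loss is small.

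**5. Bias.** Let d be the share of an arm that leaves, and g the completers' mean minus the leavers' mean.

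- Mean of all = (1 − d) × completers' mean + d × leavers' mean.
- Completers' mean − mean of all = d × g.
- Bias in the arm difference = d₁g₁ − d₂g₂. It vanishes if the two products are equal.

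The documents give neither g nor an AFEQT standard deviation, so the gap is assumed in SD units, with leavers differing from completers in one arm only:

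| Assumed gap | Shift at 10% dropout | Shift at 20% dropout (assumed) |
|---|---|---|
| 0.25 SD | 0.025 SD | 0.05 SD |
| 0.50 SD | 0.05 SD | 0.10 SD |
| 1.00 SD | 0.10 SD | 0.20 SD |

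**The case against.** The text and the schedule agree with each other and with the endpoint, so nothing is contradicted. The 10% is an allowance made for the primary endpoint. Nothing in the article says that recurrence leads to withdrawal: repeat ablation, cardioversion and drug escalation are counted as events within follow-up. The possible bias is modest even under one-sided assumptions, and the documents give no important difference for AFEQT to judge it against. All of this stands, and it limits the priority of the point.

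Two stronger readings are tempting, and the documents support neither.

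- A reader might infer from the blank discontinuation cell in the row "Presence of recurrent AF (subjective/objective" that recurrence also goes unassessed in leavers. It does not. A 12-lead ECG, symptoms and medications are marked at that visit. Portable ECG recording starts the day after discharge, with biweekly and symptom-triggered transmissions. The core laboratory judges rhythm endpoints from these recordings. The blank cell therefore costs little or no endpoint information.
- A reader might infer that imputation would have only the baseline score to work from, or that the bias could not be examined at all. That goes too far. Documented recurrence and its timing, repeat procedures, drug use and symptoms could all enter an imputation model, and the article provides for multiple imputation and sensitivity analyses if missingness is substantial. What would be lacking is any post-baseline quality-of-life score from the leavers themselves.

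The remedy is also partial. An exit score is not a month-12 score, and a 6-month score does not help those who leave earlier.

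**Conclusion.** The point holds as a minor weakness of the schedule for one key secondary endpoint. A participant who leaves before the 12-month window has no post-baseline AFEQT or EQ-5D-5L score and is excluded from the default analysis. The number is at most about 25 per arm at the plan's dropout rate. The size and direction of any bias are unknown. The shift of 0.025 to 0.10 SD rests on assumed gaps of 0.25 to 1.0 SD, confined to one arm, at 10% dropout. It would be smaller if leavers differed from completers in the same direction in both arms, and nil if share times gap were equal in the two arms. The primary endpoint, the rhythm data and the sample size are not affected.

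**What to change.** In the Quality of life section and in Table 2, add AFEQT and EQ-5D-5L at the discontinuation visit and at the existing 6-month visit. Keep the change from baseline to month 12 as the endpoint. For quality of life, use the added scores in the missing-data model, for example multiple imputation or a repeated-measures model, in place of complete-case analysis alone. An exit score should enter with its actual timing and should not stand in for the month-12 value.

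The cost is a few minutes per participant at visits that already take place, plus a schedule amendment. It is best done early, because scores not collected at these visits cannot be recovered later.
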